### Secondary and tertiary endpoints

The secondary measurement outcome will comprise the intraoperative findings and postoperative factors. As concerns the long-term postoperative complications of the mesh procedures, we will determine the extrusion rate, the presence of de novo urge symptoms (DNUS) or urinary tract infection (UTI), and the need for reoperation. The diagnosis of DNUS will be set if detrusor pressure changes are detected in cystometrographic pressures after the surgeries. The postoperative complications that will lead to reoperation will be infection, recurrent descent or incontinence, implant extrusion, chronic pelvic pain, and total retention. Operative and perioperative complications (six weeks after the procedures) described after TVM vs mTVM will be collected; overall frequency within all the cases will be calculated and severity will be graded using the IUGA classification comprising all the follow-up periods [27].

The subjective cure for prolapse and incontinence will be measured with a significant enhancement of the Pelvic Organ Prolapse/Urinary Incontinence Sexual Questionnaire (PISQ-12) and Pelvic Floor Distress Inventory (PFDI) scores. The PISQ-12 and PFDI are validated to assess the impact of SUI symptoms on quality of life and sexuality and relate well to the prolapse symptoms. Previous research has demonstrated that the questionnaires correspond well with grade of prolapse and urodynamic findings [5, 13, 17]. Our research group has assessed the validity of the questionnaires in screening for subjective genitourinary symptoms (unpublished data). To guarantee blinding of the tertiary outcome, the participant will complete the questionnaire without the outcome assessor present and seal it in an envelope, which will be given to research staff. The subjective outcome assessment is largely performed by participant-completed questionnaire, thus avoiding interviewer bias.

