#### Participants considered for trial

This will be a prospective longitudinal study involving all patients successively scheduled for operation for symptomatic prolapse POP–Q grade II or III and coexisting SUI, who will be included in the study after informed consent has been obtained. Patients will be recruited in the Department of Obstetrics and Gynaecology at the University of Szeged. The study will be conducted for an estimated maximum of 18 months (between August 2016 and December 2017). Table 1 provides an overview of the patient recruitment and evaluation plan.

**Table 1 Tab1:** Schedule of assessments/data collection

Assessment	Recruitment before intervention phase	Intervention (surgery)	Follow-up				
			6 weeks	6 months	1 years	2 years	3 years
Assessment of eligibility criteria	x						
Written informed consent	x						
Gynecological examination: incontinence symptoms	x	x	x	x	x	x	x
Gynecological examination: prolapse	x	x	x	x	x	x	x
Urodynamic examination	x				x		x
Adverse events		x	x	x	x	x	x
Questionnaires: PISQ-12 and PFDI	x		x	x	x	x	x
Introital sonography	x				x		x
Urine culture	x			x	x	x	x

The symptomatic POP–Q Stage II–III (determined by the gynecological examination using the International Continence Society quantification system) [18] anterior vaginal wall prolapse is defined as the maximum extent of the prolapsed anterior and middle compartments being within 1 cm above and 6 cm below the hymen [19, 20]. According to the international POP guidelines (the EBU and NICE guidelines) [21, 22], if the condition disrupts the patient’s life and non-surgical treatment options have not helped, it should be treated surgically.

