In all cases, SUI will be visualized after a complete physical examination is performed (verified by pad test/Bonney test/two-dimensional [2D] introital sonography and urodynamic examination). The severity of SUI was assessed using the Ingelman–Sundberg classification [23]. Urodynamic examinations comprising uroflowmetry, cystometrography, the pressure-flow study, and the abdominal leak point pressure test will be performed before surgery to objectively determine the coexisting symptomatic SUI based on the international guidelines (the EBU and NICE guidelines) [21, 22]. The abdominal leak point pressure test will be used as a standardized examination method for the evaluation of SUI with urine leakage as a sign. If the intra-abdominal pressure recorded at the point of urine leakage was < 40 cmH_2_O, the origin of the SUI was set as intrinsic sphincter deficiency (ISD) [24]. In the case of ISD, preoperative pelvic floor training (PFMT) will be recommended. If the patient is unwilling to participate in PFMT or if the training was unsuccessful, we will recommend mesh surgery. This will also be the case for suspected urethral hypermobility, i.e. if the intra-abdominal pressure at the point of urine leakage was > 60 cmH2O.

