#### Exclusion criteria

Exclusion criteria are: urge, mixed incontinence or occult SUI; prolapse < grade II or > grade III POP–Q ([21, 22], https://uroweb.org/guideline/urinary-incontinence), apical or posterior compartment prolapse, dysuria (bladder tumor, neurogenic urinary bladder damage), a history of mesh use or anti-incontinence pelvic procedures; pregnancy (urine test to accomplish); lactation period not yet finished; current urinary tract or vaginal infection, menstruation on the day of examination; contraindications for measurements or interventions, for example, acute inflammatory or infectious disease, tumor or fracture; de novo systemic or local estrogen treatment (< 3 months); de novo drug treatment with anticholinergics or other bladder active substances (tricyclic antidepressants and selective serotonin reuptake inhibitors) and cancer of the pelvic organs.

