### Statistical analyses

Analysis of the patients will follow the CONSORT flow diagram (Fig. 1) through the phases of the study (enrollment [assessed, excluded, randomized], allocation [control group and experimental group with intervention received or not received], follow-up [lost to follow-up, discontinued intervention] and analysis) [30].

All statistical analyses will be conducted using SPSS software version 22 (IBM, Armonk, NY, USA). All tests will be two-sided and significance will be set at *P* < 0.05. Efficacy measurements were adjusted by intention-to-treat analysis. Missing values will be replaced using the last observation carried forward (LOCF) method. No subgroup analyses are planned. Standard deviations, 95% confidence intervals, and median will be used for the descriptive analyses. Primary and secondary outcome analysis: the Chi-square test or Fisher’s exact test will be employed to identify any objective outcome differences among groups.

Generally, continuous data will be checked for normality using the Shapiro–Wilk test. If the normality assumption is violated, then PISQ-12 and PFDI scores as tertiary outcomes will be normalized by log transformation (log10(x)). Univariate-repeated measure analysis of variance (ANOVA) will be used to determine the secondary outcome between and within the two groups (mTVM, TVM group) at six endpoints (before intervention and during follow-up clinical appointments 1–5 following intervention). Mixed design ANOVA will be carried out to determine the effects of the modified operation on subjective cure rate for POP and SUI, and the Bonferroni post hoc test will be used to test the difference between means. All statistical analyses will be completed after the final measurement of the last patient during the last clinical appointment after intervention. The repeated measure design with seven points in time allows us to monitor how patients change over time in both short-term (before/during intervention) and long-term situations (before/after intervention).

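### The harm called de novo urge symptoms is diagnosed only from a detrusor pressure change on cystometry, scheduled after surgery at 1 and 3 years, so its reported rate is not a rate of urge symptoms

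*Protocol article*

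**What the plan says.** Under Secondary and tertiary endpoints, the protocol article sets out the long-term complications to be compared: "we will determine the extrusion rate, the presence of de novo urge symptoms (DNUS) or urinary tract infection (UTI), and the need for reoperation". The next sentence gives the criterion for one of them: "The diagnosis of DNUS will be set if detrusor pressure changes are detected in cystometrographic pressures after the surgeries". No other section offers a second way of reaching the diagnosis.

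Cystometry belongs to the urodynamic work-up, described under Participants considered for trial as "Urodynamic examinations comprising uroflowmetry, cystometrography, the pressure-flow study, and the abdominal leak point pressure test". In Table 1 the row "Urodynamic examination" is marked at recruitment, 1 year and 3 years. The rows "Gynecological examination: incontinence symptoms" and "Questionnaires: PISQ-12 and PFDI" are marked at recruitment and at all five follow-up visits. Adverse events are also collected at all five. None of these three rows is tied to DNUS.

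Two further statements bear on the point. The exclusion list opens with "Exclusion criteria are: urge, mixed incontinence or occult SUI". Statistical analyses gives a general rule for gaps: "Missing values will be replaced using the last observation carried forward (LOCF) method".

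**The concern.** The endpoint is named for something a woman feels and reports, but it is decided by a pressure tracing. These are different measurements, and each can be present without the other. The tracing is also taken less often than symptoms are recorded.

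DNUS is one of the few harms named for comparing the two operations. The Background expects complication rates similar to those of the original mesh, and the safety section states that the modification carries no higher risk. A reader of the results will take the DNUS line as evidence on urge symptoms, although it was not built to measure them.

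**Working it through.** The plan states no figure for DNUS, so there is none to reproduce. The check sets the definition against the schedule.

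**Step 1: what is measured when (Table 1)**

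| Visit | Incontinence symptoms | Adverse events | Questionnaires | Urodynamics (cystometry) |
|---|---|---|---|---|
| Recruitment | yes | no | yes | yes |
| 6 weeks | yes | yes | yes | no |
| 6 months | yes | yes | yes | no |
| 1 year | yes | yes | yes | yes |
| 2 years | yes | yes | yes | no |
| 3 years | yes | yes | yes | yes |

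The DNUS criterion can be met at 2 of 5 scheduled follow-up visits and cannot be met at the other 3.

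**Step 2: who is counted at a visit with cystometry**

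| | Pressure change | No pressure change |
|---|---|---|
| New urge symptoms | counted, correctly | not counted |
| No urge symptoms | counted as DNUS | not counted, correctly |

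The definition errs in both off-diagonal cells, in opposite directions.

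**Step 3: urge that starts at a visit without cystometry**

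- It persists with a pressure change: found at 1 year if it began at 6 weeks or 6 months, and at 3 years if it began at 2 years. The case is kept and only its timing is lost.
- It resolves before the next cystometry: lost.
- It persists without a pressure change: lost.

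**Step 4: effect on the comparison**

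Let p be the true proportion with new urge symptoms, s the share of those women who are counted, and f the share of symptom-free women who are counted. The reported proportion is s·p + f·(1 − p).

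If s and f are the same in both arms, the reported difference is (s − f)(p₁ − p₂), which is smaller than the true one whenever s − f lies between 0 and 1. If s or f differs between arms, the reported difference can move either way. The documents give no value for p, s or f and do not show that s and f are equal across arms. Neither direction nor size can therefore be derived from them.

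**Step 5: missing cystometry**

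Urge and mixed incontinence are excluded at entry, so a woman starts as DNUS-absent. If she misses the 1-year cystometry and carrying forward is applied, the value carried is that baseline absence. She then enters the count as an observed negative although she was never examined after surgery.

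**The case against.** The strongest defence is that an objective criterion was a reasonable choice. Under Concealment of group allocation from participants, women learn their allocation after the 12-month forms (earlier if a major complication occurs), while the outcome assessor is meant to stay blinded. A pressure tracing read by a blinded assessor is less open to bias than a symptom reported at 2 or 3 years by a woman who knows her operation. The endpoint is also listed as long-term, so losing brief early urge matters less, and urge complaints can still surface as adverse events or in the questionnaires. All of this stands. It argues for keeping the cystometric result, but not for calling it a symptom rate. Complaints recorded elsewhere do not enter the DNUS count.

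The criterion is worded with a plain if, not only if. That is true, but it is the only criterion given.

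Three stronger readings are tempting and are not supported:

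- **Every new urge symptom at 6 weeks, 6 months or 2 years is lost.** Step 3 shows that persistent urge with a pressure change is found at the next cystometry.
- **The DNUS count at 6 weeks and 6 months is zero by construction.** That needs carrying forward to be applied at visits where no cystometry is scheduled. The rule speaks of missing values, and the article does not say that an unscheduled examination is one. No 6-week or 6-month DNUS count is announced.
- **The trial loses a stated amount of power to detect a safety difference, or the comparison is biased toward similarity.** One can assume true rates of 10% and 25%, with half the cases captured and no false positives. The reported rates are then 0.5 × 10% = 5% and 0.5 × 25% = 12.5%, and chi-square power at 65 per arm falls from 62% to 33%. Every input except the arm size is assumed. The plan claims no power for DNUS, the risk ratio is 2.5 in both cases, and false positives are ignored.

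**Conclusion.** The point holds as a mismatch between the name of a secondary harm and its criterion. The reported DNUS rate would be the rate of a cystometric finding at 2 of 5 follow-up visits. It omits symptomatic women without a pressure change and those with transient urge, and it includes symptom-free women with a pressure change. This follows from the endpoint definition and Table 1 alone. It assumes only that the stated criterion is the one used.

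How many women are misclassified, and whether the comparison between arms shifts, cannot be known from the documents. The consequence is limited: the primary outcome and the sample size are unaffected, and persistent urge with a pressure change is not lost. The concern about missing cystometry applies to women without a postoperative examination if baseline absence is carried forward for them.

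**What to change.** Replace the single DNUS outcome with two separately named ones:

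1. **New urge symptoms**, taken from the incontinence-symptom assessment at each of the five follow-up visits and compared with the same assessment at recruitment. State that urge is recorded there, because the Table 1 row mentions only incontinence symptoms and the exclusion criterion does not clearly cover urgency without leakage. Make the visits up to 12 months the main comparison, since participants are told their allocation after the 12-month forms. Report 2 and 3 years as supportive.
2. **De novo detrusor finding on cystometry**, at 1 and 3 years.

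For the second outcome, do not carry baseline absence forward as an observed negative for a woman without a postoperative cystometry. Give the number examined in each arm as the denominator.

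Cost: no new test or visit. It is more than a wording change if urge is not already recorded in the symptom assessment. The record form would then need an explicit item, and women enrolled since recruitment began in August 2016 might lack a baseline entry, which should be reported. The symptom outcome is less objective, and at 2 and 3 years it comes from unblinded participants, which is why the cystometric result stays beside it.

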Therefore, the research group developed a modification to the transobturator four-arm TVM [13, 17] to increase its anti-incontinence effect. While the sling is located beneath the mid-urethra, the TVM elevates the distal part of the anterior vaginal wall [13, 17]. In the original TVM, the posterior part of the mesh is anchored to the anterior aspect of the cervix and the anterior arms are spread under the bladder neck with stabilizing sutures. We hypothesize that the original TVM operation can be followed by residual SUI since the strengthening of the back arms may result in a backward dislocation of the entire mesh. The posterior movement of the mesh allows the dorsal rotation of the urethra since the mid-urethra is not suspended. The proposed modification to the original surgical procedure includes the suture of the anterior part of the mesh to the mid-urethra to prevent the mesh sliding. We think that the appropriate elevation of the mid-urethra would thus occur with the anterior arms and that would achieve a more effective anti-incontinence. The pubourethral ligament is usually loose in SUI, but the anchored mesh would theoretically normalize its function and stabilize the urethra. Intra- and postoperative complication rates would be expected to be similar to those with the original four-arm TVM, but the modified TVM with the anchoring suture would be slightly superior with respect to POP repair and remarkably more effective in SUI correction. In our preliminary study, the anterior fixing of the TVM to the mid*-*urethra demonstrates as high an efficacy of anti-incontinence as 96.8% and an enormously reduced recurrence prolapse rate of 3.2% in (unpublished data). The mesh extrusion rate is particularly low and this may be due to the fact that the stabilizing sutures exert a lack of “folding/wrinkling” of the edge of the mesh, preventing a lifting up of the mesh which does not compress the mucosa and derange the periprosthetic vasculature.

A further modification to the TVM surgery is that the positioning of the mesh will occur 1.5 cm below the urethral meatus, leading to an elevation of the entire anterior vaginal wall including the anterior and middle compartments as well. By contrast, the original TVM surgery does not prevent anterior compartment prolapse [13, 17].

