### Primary endpoints

The primary outcome measures will be a significant improvement in POP repair and objective cure of SUI after the surgery. The efficacy of POP repair will be understood as a significant (> 3 cm) improvement during follow-up at points Aa, Ba, C, and D using the POP–Q system (International Continence Society) [19, 20]. Anti-incontinence efficacy is classified as no further SUI, as diagnosed by cough tests and urodynamic examinations. Besides the gynecological and urodynamic examinations, sonographic findings from introital ultrasound examinations will be analyzed in terms of anatomical success both before and following surgery and during follow-up.

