### Assessment of safety: postoperative complications/reoperations

In the current study, there are no anticipated risks or inconveniences, as the examinations and intervention employed are well-known and widely used in pelvic floor defect surgery. The modification to the TVM surgery does not carry a higher risk for patients than that of the original TVM in the setting of a fully equipped operation theatre. This makes the immediate detection and treatment of adverse events possible. Also, after leaving the operation room, all patients will be closely monitored for the occurrence of potential (severe) adverse events (short-term postoperative complications) on the postoperative intensive ward. Moreover, the inclusion of each individual patient in the study is indicated in the electronic hospital information system and, hence, is visible to all physicians and nurses involved in the care of the patient. This facilitates the reporting of (severe) adverse events to the principal investigator. The principal investigator will report suspected unexpected serious adverse reactions to the Institutional Review Board.

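### The reoperation outcome is classed as a mesh complication but counts reoperation for recurrent incontinence or prolapse, so it moves with the primary endpoint as well as with mesh harm

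*Protocol article*

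**What the plan says.** Under Secondary and tertiary endpoints, the protocol article introduces the long-term complications of the mesh procedures and says "we will determine the extrusion rate, the presence of de novo urge symptoms (DNUS) or urinary tract infection (UTI), and the need for reoperation". It then names the reasons: "The postoperative complications that will lead to reoperation will be infection, recurrent descent or incontinence, implant extrusion, chronic pelvic pain, and total retention". The later heading "Assessment of safety: postoperative complications/reoperations" also places reoperation under safety.

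Under Primary endpoints, continence success is defined thus: "Anti-incontinence efficacy is classified as no further SUI, as diagnosed by cough tests and urodynamic examinations". The prolapse part reads: "The efficacy of POP repair will be understood as a significant (> 3 cm) improvement during follow-up at points Aa, Ba, C, and D".

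The Background expects two things of mTVM. SUI correction should be much better than with the original operation, and on safety: "Intra- and postoperative complication rates would be expected to be similar to those with the original four-arm TVM". Sample size calculation puts the SUI cure rates at 92% for mTVM and 72% for TVM. Under Statistical analyses, for primary and secondary outcomes, a chi-square or Fisher's exact "test will be employed to identify any objective outcome differences among groups".

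**The concern.** Take two women. One has no mesh problem but leaks again and is reoperated for incontinence. The other is dry and is reoperated for total retention. Under the stated list each has one complication leading to reoperation. The first woman has already been counted as a primary-endpoint failure.

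An outcome built this way responds to two things: mesh harm and lack of cure. The trial expects the first to be similar between arms and the second to differ by 20 percentage points. A lower reoperation rate with mTVM could therefore come from better continence alone and be read as fewer complications. Conversely, an excess of harm-related reoperation with mTVM could be partly or wholly offset by fewer reoperations for incontinence. Either way, the outcome cannot show whether complications are similar, which is what the Background expects.

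**Working it through.** **Inputs from the protocol article.** SUI cure is 72% (TVM) and 92% (mTVM), so non-cure is 28% and 8%. There are 65 women per arm (Abstract; also the 130 in Sample size calculation before inflation). Tests are two-sided at 0.05, by chi-square or Fisher.

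**Plan's own figure.** No stated figure exists for reoperation. The 130 fits the two cure rates if Fisher's exact test is used: 128 women give 80.6% power and 130 give 81.4%. This only supports using 28%, 8% and 65 per arm below.

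**Assumptions, because the article gives neither.** f is the share of SUI failures that are reoperated. h is the rate of reoperation for infection, extrusion, pain or retention. The two causes are treated as independent, and all SUI non-cure is taken as eligible for the recurrence reason. Prolapse failures are left out.

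**Failures available to feed the outcome.** TVM: 65 × 0.28 = 18.2 women. mTVM: 65 × 0.08 = 5.2 women.

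**Formula.** All-cause reoperation = 1 − (1 − f × non-cure)(1 − h).

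**Equal harm, h = 5% in both arms**

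| f | TVM | mTVM | mTVM − TVM |
|---|---|---|---|
| 10% | 1 − 0.972 × 0.95 = 7.7% | 1 − 0.992 × 0.95 = 5.8% | −1.9 points |
| 25% | 1 − 0.930 × 0.95 = 11.7% | 1 − 0.980 × 0.95 = 6.9% | −4.75 points |
| 50% | 1 − 0.860 × 0.95 = 18.3% | 1 − 0.960 × 0.95 = 8.8% | −9.5 points |

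Harm-related reoperation alone is 5% against 5% in every row. By exact enumeration with 65 per arm, the probability of significantly fewer reoperations with mTVM is 0.06, 0.15 and 0.35 by chi-square, and 0.025, 0.09 and 0.27 by Fisher. When the arms do not differ (5% each, f = 0), the same probability is 0.023 by chi-square and 0.006 by Fisher.

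**Unequal harm, TVM against mTVM**

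| f | harm 5% vs 10% | harm 5% vs 15% |
|---|---|---|
| 10% | 7.7% vs 10.7% | 7.7% vs 15.7% |
| 25% | 11.7% vs 11.8% | 11.7% vs 16.7% |
| 50% | 18.3% vs 13.6% | 18.3% vs 18.4% |

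Approximate break-even is f = harm excess ÷ 0.20. A 5-point excess cancels at 0.05 ÷ 0.20 = 25% and reverses above that. A 10-point excess cancels at 0.10 ÷ 0.20 = 50%. For harm of 5% vs 15%, chi-square power is 0.49 on harm-related reoperation alone and about 0.05 on the mixed outcome at f = 50%.

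**The case against.** Five arguments stand against the point.

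- **All-cause reoperation is a legitimate outcome.** It matters to patients whatever its reason. This stands. The fault is presenting it undivided as a mesh complication.
- **Other items would show harm.** A reader might infer that an excess of pain, infection or retention could appear nowhere else. The article does not support that. Extrusion, DNUS and UTI have their own items. Morbidity graded by the IUGA classification is a named secondary endpoint in the Abstract and covers all follow-up periods. Table 1 records adverse events at surgery and at all five follow-up visits. An extrusion excess in particular would show in the extrusion rate.
- **The numbers rest on chosen shares.** This stands. At a 10% share the built-in gap is only 1.9 points, and full masking of a 5% vs 15% difference needs a share near 50%. Nor are the probabilities of a significant result inflated false-positive error: all-cause reoperation truly differs in those scenarios, so they are power for a real difference that may be misread as safety.
- **No decision depends on it.** A reader might infer that the trial would recommend mTVM if continence improves without more complications. No such rule is written. The Discussion ties possible adoption to success in treating SUI, and similar complication rates are an expectation without a formal test.
- **A breakdown by cause is reporting detail that a condensed article may omit.** This stands only in part. A table layout may be left to a fuller document, but the article itself classifies recurrent descent and incontinence as complications and places reoperation under safety.

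**Conclusion.** The point holds for one secondary outcome. As classified, need for reoperation combines failure of the primary endpoints with mesh and surgical harm. Under the trial's own expected cure rates it leans towards mTVM when harm is equal. With 5% harm-related reoperation per arm, the lean is 1.9, 4.75 or 9.5 points if 10%, 25% or 50% of SUI failures are reoperated. The same mechanism can dilute, cancel or reverse a true excess of harm-related reoperation.

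The direction follows from the article's cure rates. The size rests on the assumed share and harm rates, on independence of the two causes, and on treating all SUI non-cure as possible recurrence; it is small if few failures are reoperated. The distortion reaches the reoperation outcome and any overall complication count that includes it, and goes no further. The primary analysis is not affected. This is a worthwhile, inexpensive improvement.

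**What to change.** In Secondary and tertiary endpoints, report reoperation by cause:

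1. Place reoperation for recurrent incontinence or recurrent descent with the efficacy outcomes and leave it out of the complication count.
2. Base the between-arm safety comparison on reoperation for infection, implant extrusion, chronic pelvic pain or total retention.
3. Keep all-cause reoperation as a separately labelled patient-relevant outcome.

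The reasons are already listed, so the cost is a change of endpoint wording and an added table row, provided the reason for each reoperation is recorded. The drawback is fewer events in the safety category and so a wider confidence interval. The change concerns classification and reporting only and does not alter when a patient is reoperated.

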### Inclusion and exclusion criteria

#### Inclusion criteria

Female adults aged > 40 years with coexisting pelvic floor defects will be recruited, at least one year following delivery, irrespective of parity and pre- or postmenopausal state, medically and physically fit for the measurement and therapeutic surgeries, and, in the case of systemic or local estrogen treatment, stable for the past three months before inclusion.

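### Subjective cure of prolapse and leakage rests partly on a sexual-function questionnaire in women not selected for sexual activity, and LOCF could hide women who stop after surgery

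*Protocol article*

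**What the plan says.** - **Endpoint.** Under Secondary and tertiary endpoints: "The subjective cure for prolapse and incontinence will be measured with a significant enhancement of the Pelvic Organ Prolapse/Urinary Incontinence Sexual Questionnaire (PISQ-12", with the PFDI scores named alongside. The same section describes the instruments: "The PISQ-12 and PFDI are validated to assess the impact of SUI symptoms on quality of life and sexuality and relate well to the prolapse" (quoted short of the sentence's last word).
- **Population.** Inclusion criteria: "Female adults aged > 40 years with coexisting pelvic floor defects will be recruited", "irrespective of parity and pre- or postmenopausal state". Neither these criteria, the Exclusion criteria (which begin "urge, mixed incontinence or occult SUI; prolapse < grade II or > grade III POP–Q") nor the section on participants considered for the trial mentions sexual activity.
- **Schedule.** The row "Questionnaires: PISQ-12 and PFDI" in Table 1 is marked at baseline, 6 weeks, 6 months, 1 year, 2 years and 3 years, with no restriction on who completes it.
- **Analysis.** Statistical analyses applies intention-to-treat and adds "Missing values will be replaced using the last observation carried forward (LOCF) method" and "No subgroup analyses are planned". Subjective cure of prolapse and incontinence is to be compared by mixed-design ANOVA.
- **Rank.** The Abstract lists subjective cure as secondary. Statistical analyses calls the PISQ-12 and PFDI scores tertiary.

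**The concern.** The endpoint and the population do not fit each other. The target is relief of prolapse and leakage as the woman perceives it, yet part of the measure is a score for sexual function. The trial takes women over 40 before or after the menopause without asking whether sexual function can be assessed in them.

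Two things are at stake. First, the measure of cure means something different, or is unavailable, in some of the randomised women. Second, sexual activity can change after randomisation because of the operation itself. The Background names dyspareunia and chronic pelvic pain among the common complications of mesh, and the two arms differ in where the mesh lies and how it is fixed. If a woman stops sexual activity because of pain and leaves the PISQ-12 blank, the stated missing-data rule substitutes a score from before she stopped. That can make an unfavourable course look neutral or favourable, possibly to a different degree in the two arms.

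**Working it through.** **1. The plan's own figure.** None exists for the PISQ-12. The total of 130 under Sample size calculation is set on objective SUI cure. With 92% versus 72%, two-sided 0.05 and 65 per arm, Fisher's exact test has 81.4% power (80.6% at 64 per arm). So 130 belongs to the objective outcome, and nothing below changes it.

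**2. The stated rules applied to four kinds of participant.** There are six questionnaire points: baseline plus five follow-ups.

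| Woman | Baseline PISQ-12 | What the stated rules give |
|---|---|---|
| Active throughout | Present | A change in sexual function; PFDI also available |
| Not active throughout | May be blank | If blank, no earlier value for LOCF and no change from baseline; if answered, the score says little about leakage or prolapse |
| Not active at baseline, resumes | May be blank | A later score with no baseline to compare |
| Active at baseline, stops after surgery and leaves the form blank | Present | LOCF carries the last score from before she stopped |

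In the last row, a woman who completes the 6-week form and then stops has 5 − 1 = 4 of her five follow-up values filled from that one visit. If it showed improvement, the improvement is held to 3 years. If she stops before 6 weeks, her baseline is carried and she appears unchanged.

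The PFDI column would be filled in all four rows: nothing in the documents makes the PFDI depend on sexual activity.

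**3. Precision of a PISQ-12 analysis in active women (illustration only).** The documents give no share of sexually active women, so the shares are assumed. The detectable standardised difference at 80% power, two-sided 0.05, is d = (1.96 + 0.84) × √(2/m), where m is the number per arm with a usable score.

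| Assumed share active | m of 65 per arm | d | m of 81 per arm | d |
|---|---|---|---|---|
| 100% | 65 | 0.49 | 81 | 0.44 |
| 90% | 58.5 | 0.52 | 72.9 | 0.46 |
| 70% | 45.5 | 0.59 | 56.7 | 0.53 |
| 50% | 32.5 | 0.69 | 40.5 | 0.62 |
| 30% | 19.5 | 0.90 | 24.3 | 0.80 |

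These figures show the price of a clean PISQ-12 analysis set. They do not estimate bias in the present plan.

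**The case against.** The strongest reply has four parts.

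- **Validity.** The article asserts that both instruments are validated and refers to the group's own unpublished validation. A reader might infer that women who are not sexually active cannot be scored validly. The documents do not support that: they give neither the items nor the scoring rules of the PISQ-12. What stands is narrower. The validity statement does not address such women, and an instrument described as covering sexuality is an indirect gauge of leakage or prolapse in them.
- **No joint rule.** A reader might infer that each woman must improve on both scales, so that some could never be counted as cured. The text states no per-woman threshold and no rule for combining the scores. The planned ANOVA compares means, although the article also speaks of a cure rate. Every woman keeps the PFDI.
- **Harms are recorded elsewhere.** Adverse events are collected at every visit, complications are graded over all follow-up, and chronic pelvic pain is listed as a reason for reoperation. This softens the safety side. It does not stop the questionnaire comparison itself from looking better than the women's course.
- **An article condenses.** Scoring of inapplicable items may be left to the full protocol or SAP. That is fair for scoring detail. But the endpoint, the unrestricted schedule, LOCF and the absence of subgroup analyses are stated here, and the mismatch lies between those stated choices.

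A reader might also infer that women who stop sexual activity drop out of the comparison. Under the stated LOCF rule, a woman with an earlier score is carried forward, and that is the problem described here.

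**Conclusion.** The point holds as a mismatch between a stated endpoint and the stated population, made worse by LOCF for women who stop sexual activity after surgery. It is worth correcting but limited in reach. It affects subjective cure, ranked secondary or tertiary, and leaves the objective SUI and prolapse outcomes and the sample size as they are. The Hypothesis section does name the questionnaire within the alternative hypothesis for the primary outcome, so the result may be read with the main finding, but Primary endpoints contains no questionnaire.

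The size cannot be derived. The documents give no share of women who are not sexually active, no rate of stopping after surgery and no difference between arms; any count of affected women would be multiplication of an assumption. The conclusion assumes that some women admitted are not sexually active, or stop during follow-up, and that some of them leave the PISQ-12 blank. The criteria permit this, but the documents do not show how often it happens.

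**What to change.** 1. Define subjective cure of prolapse and incontinence by the PFDI, in all randomised women.
2. Record sexual activity (yes/no, with the reason if stopped) at baseline and at each follow-up visit.
3. Analyse the PISQ-12 as a separate sexual-function outcome in women sexually active at baseline. That set is fixed before surgery, so the randomised comparison is kept. Do not carry scores forward across stopping.
4. Report stopping because of pain or prolapse symptoms by arm, as an unfavourable outcome.

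The cost is one item per visit, revised wording of the endpoint and analysis set, and lower precision for the PISQ-12 (for example 0.69 instead of 0.49 standard deviations detectable if half of 65 per arm were active, an assumed share). Recruitment began on 22 August 2016, so baseline activity of women already enrolled would have to be recovered from their existing forms or notes. All analyses wait for the last patient's final visit, so the wording can still be settled beforehand.
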